**Secondary Objectives:**

- To obtain estimates of the change in chemotherapy-induced peripheral neuropathy (CIPN) severity
- To elucidate the mechanisms of acupuncture by obtaining estimates of tactile threshold, vibration threshold, thermal threshold and controlled pain modulation. To obtain estimates of the change in insomnia, anxiety and depression, and fatigue symptoms.
- To obtain estimates of the correlation of treatment expectancy and treatment response among patients who undergo acupuncture or sham acupuncture.
- To estimate the proportion of patients with a dose reduction and the proportion with a dose escalation of neuropathy medication during the course of the 12 weeks.

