## **6.0 CRITERIA FOR SUBJECT ELIGIBILITY**

### **6.1 Subject Inclusion Criteria**

- English-speaking
- Age  $\geq$  18 years old
- Solid tumor survivors with no evidence of disease
- Moderate to severe CIPN, defined by symptoms such as numbness, tingling, or pain ratings of 4 or greater on a 0-10 numeric rating scale (NRS)
- Have completed neurotoxic chemotherapy at least 3 months prior to enrollment
- If taking anti-neuropathy medications, they are on a stable regimen (no change in 3 months)

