### **NCI –CTC 4.0**

The National Cancer Institute (NCI) of the National Institutes of Health (NIH) has published standardized definitions for adverse events (AEs), known as the Common Terminology Criteria for Adverse Events (CTCAE, also called "common toxicity criteria"), to describe the severity of organ toxicity for patients receiving cancer therapy. Toxicity is graded as mild (Grade 1), moderate (Grade 2), severe (Grade 3), or life-threatening (Grade 4), with specific parameters according to the organ system involved. Death (Grade 5) is used for some of the criteria to denote a fatality. Severity of CIPN defined by NCI-CTC 4.0 is detailed in Appendix B. CIPN severity will be assessed at baseline and weeks 8 and 12. The CIPN grade for the baseline measure can be obtained from the patients EMR if it was measured within two weeks of the consent/baseline visit.

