## **12.0 CRITERIA FOR THERAPEUTIC RESPONSE/OUTCOME ASSESSMENT**

The primary endpoint will be measured by NRS of the most bothersome CIPN symptom and measured at time of consent (baseline) and at 8 weeks, after the final acupuncture session for the acupuncture or sham acupuncture arms and at baseline and after 8 weeks of usual care for patients randomized to the usual care arm. Secondary endpoints will be measured by the FACT/GOG-NTx, NPS, NCI-CTC 4.0, ISI, HADS, BFI, TES, QST, and CPM. Additionally, NRS will be assessed as a secondary aim at baseline, 4 weeks, and 12 weeks for all arms. All non-NRS secondary endpoints will be assessed at baseline, 8 weeks and 12 weeks. The NPS and FACT-GOG/NTX will also be assessed at 4 weeks.

All patients enrolled in the study who completed acupuncture or sham acupuncture will be included in the analyses, and any patients who withdraws from the study or who is lost to followup will be described.

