### **14.0 BIOSTATISTICS**

The main objective of this study is to provide preliminary data on the effect of acupuncture in reducing persistent CIPN symptoms from baseline to after 8 weeks of acupuncture or sham acupuncture as compared to a usual care control in order to design a fully powered randomized trial of acupuncture versus sham acupuncture. The enrollment goal is 75 patients.

To help plan the definitive trial, we will derive estimates for the standard deviation of all endpoints and the correlation between baseline and follow-up for each endpoint. For each of the patient reported outcomes (NPS, FACT/GOG-NTx, NRS) analysis will be by ANCOVA with the baseline score and most bothersome CIPN symptom as covariates.. Treatment will be coded as dummy variables for any treatment and real acupuncture, hence the three groups will be coded 1/1, 0/1, and 0/0 for acupuncture, Sham acupuncture, and UC respectively. Similarly, to account for type of most bothersome CIPN symptom (tingling vs numbness vs pain) dummy variables for tingling, numbness, and pain will be coded 1/0, 0/1, and 0/0, respectively. Where the week of follow-up is given in the subscript, we will calculate:  $NRS_8 = \beta_1 NRS_0 + \beta_2 \text{Real Acupuncture} + \beta_3 \text{Any Acupuncture} + \beta_4 \text{Tingling} + \beta_5 \text{Numbness} + c$ . The primary endpoint will be NRS of the most bothersome CIPN symptom at 8 weeks.

We will estimate the change in the proportion of patients with a CIPN severity of grade 3 or higher according to the NCI-CTC 4.0 from baseline to 8 and 12 weeks along with an exact 95% confidence interval, separately. To explore the relationship between quantitative sensory testing (QST) and

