## **15.2 Randomization**

Randomization is implemented via MSKCC's Clinical Research Database (CRDB), a secure system that ensures that treatment allocation cannot be guessed before or modified after a patient is registered on trial, allowing for full allocation concealment. Randomization will be 1:1:1 (ACU:Sham: UC) using randomly permuted blocks of random length stratified by type of the most bothersome CIPN symptom (tingling vs numbness vs pain) and severity of such symptom (moderate 4-6 vs 7-10 on NRS). Once the patient is randomized, the CRS or CRM will inform the acupuncturist of the patient's group assignment and the RSA of whether the patient was assigned to an acupuncture group or to the UC group. The RSA's and patients will be blinded to which acupuncture group the patient was assigned. The acupuncturists will be the only ones unblinded. The rest of the study co-investigators and staff will remain blinded.

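### The only planned NCI-CTC summary, the change in the proportion at grade 3 or higher, cannot show improvement in any patient who enters at grade 2 or below, and entry sets no minimum CTC grade

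*Protocol*

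**What the plan says.** **Entry.** Section 6.1 admits patients with "Moderate to severe CIPN, defined by symptoms such as numbness, tingling, or pain ratings of 4 or greater" on the 0-10 NRS. Neither the inclusion nor the exclusion criteria mention a CTC grade.

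**Stratification.** Section 15.2 stratifies by type of most bothersome symptom and by "severity of such symptom (moderate 4-6 vs 7-10 on NRS". Patients in the lower NRS band are therefore an intended part of the sample.

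**CTC scale.** The NCI-CTC 4.0 paragraph of Section 8.0 gives the general key: "Toxicity is graded as mild (Grade 1), moderate (Grade 2), severe (Grade 3), or life-threatening (Grade 4". It refers to Appendix B for the neuropathy criteria and schedules the grade at baseline, week 8 and week 12.

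**Role.** Section 2.0 lists as a secondary objective "To obtain estimates of the change in chemotherapy-induced peripheral neuropathy (CIPN) severity". Section 12.0 names the CTC grade among the secondary endpoints: "Secondary endpoints will be measured by the FACT/GOG-NTx, NPS, NCI-CTC 4.0, ISI, HADS, BFI, TES, QST, and CPM".

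**Analysis.** Section 14.0 states "We will estimate the change in the proportion of patients with a CIPN severity of grade 3 or higher according to the NCI-CTC 4.0", at weeks 8 and 12, with an exact 95% confidence interval. The protocol describes no other summary of the CTC grade.

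**The concern.** The trial sets out to recruit moderate as well as severe neuropathy, yet the CTC analysis is cut at the grade that the protocol's own key labels severe. A patient below that cut at baseline has nowhere to go on this measure except up. A move from grade 2 to grade 1 or 0, which is the kind of benefit the trial hopes to see, leaves the reported proportion unchanged.

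The stake is how the pilot's CTC result will be read. Its stated purpose is to inform a definitive trial. If the proportion at grade 3 or higher barely changes, there are two possible reasons: the grades did not improve, or few patients were in a position to register improvement. The planned summary cannot tell these apart. Section 14.0 chooses this cut positively, so it is not a detail simply left open for a later analysis plan.

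**Working it through.** The protocol states no expected rate, precision or power for the CTC endpoint, so there is no figure of its own to reproduce. The check is a count.

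**Step 1: the identity.** In a group of *n* patients with both assessments, let *a* be the number at grade 3 or higher at baseline, *b* the number of those who are below grade 3 at follow-up, and *c* the number who start below grade 3 and are at grade 3 or higher at follow-up.

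- Baseline proportion: a/n
- Follow-up proportion: (a − b + c)/n
- Change: (c − b)/n

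Since *b* cannot exceed *a*, the change can never be lower than −a/n. The n − a patients who start below grade 3 enter only through *c*, which counts worsening. This holds whatever the grade mix.

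**Step 2: what the cap means for 25 per arm.** The group size of 25 is from Section 14.0. The baseline share at grade 3 or higher is **an assumption**, because the protocol does not give it. A wide range is shown in whole patients (2.5 is taken as 2 and 7.5 as 8).

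| Assumed share | At grade 3+ (a) | Cannot register improvement (25 − a) | Largest possible fall (a/25) |
|---|---|---|---|
| about 10% | 2 | 23 | 8 points |
| 20% | 5 | 20 | 20 points |
| about 30% | 8 | 17 | 32 points |
| 40% | 10 | 15 | 40 points |
| 60% | 15 | 10 | 60 points |

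The cap itself would be imprecisely known. The exact (Clopper-Pearson) 95% interval for the baseline proportion alone is 1% to 26% at 2 of 25, and 15% to 54% at 8 of 25.

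**Step 3: pooled over 75.** If the change is estimated over the whole sample, the proportional cap is the same. At a 20% share, 15 of 75 start at grade 3 or higher, 60 cannot register improvement, and the largest possible fall is 15/75 = 20 points.

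**Step 4: an illustration of what is lost.** Suppose that in an arm of 25, 5 patients enter at grade 3 and 20 at grade 2. Suppose also that all 20 grade 2 patients improve to grade 1 and the 5 grade 3 patients do not change. Then b = 0 and c = 0, so the planned summary is (0 − 0)/25 = 0. The proportion improved by at least one grade is 20/25 = 80%. Its exact 95% interval is 59.3% to 93.2%, the complement of 6.8% to 40.7% for 5 of 25. The example is hypothetical and deliberately extreme. It shows that the two summaries of the same collected data can disagree completely.

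**The case against.** The case on the other side is substantial, and much of it limits the point.

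- **No link between the scales.** A reader might infer that most patients with NRS 4-6 are grade 2 and so start below the cut. The protocol does not support this. The NRS is a patient rating and the CTC grade a separate assessment. The grade labels come from a general description of organ toxicity, and the neuropathy criteria are in Appendix B, whose content is not in the text available. No mapping and no expected grade distribution is given. A patient with NRS 4-6 could be grade 3, and one with NRS 7-10 could be grade 2. This objection stands, so the point is confined to patients who enter at grade 2 or below, however many they are.
- **No test is planned.** A reader might also count how many grade 3 patients must improve before a paired test reaches significance. That is the wrong yardstick. Section 14.0 plans an estimate with an interval, makes no power claim for this endpoint, and does not clearly say that the estimate is by arm. This stands too.
- **Severity is measured elsewhere.** The primary endpoint is the NRS at week 8. NRS, NPS and FACT/GOG-Ntx are analysed on their full scales by ANCOVA, where patients with moderate symptoms can improve. The future sample size rests on the standard deviation of the CIPN score and its correlation with baseline, not on this proportion. Section 4.1 does not even list the CTC grade among the secondary endpoints, although Section 12.0 does. This bounds the consequence but does not remove it: those three scales are patient-reported, and none of them replaces the CTC grade.
- **A shift table could come later.** A grade distribution could be added in an analysis plan or report, and tracking severe grades is a recognisable descriptive choice. That is fair. Even so, Section 14.0 names the cut as the CTC analysis, so the better summary should be named there.

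**Conclusion.** The point holds in a limited form. As written, the sole CTC summary is blind to improvement in anyone who enters at grade 2 or below and registers only worsening in those patients. This follows from the definition and needs no assumption.

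The size is not derivable from the protocol, because the baseline grade mix is not stated. Across an assumed share at grade 3 or higher of about 10% to 60%, the number per arm of 25 who could not register improvement runs from 23 down to 10. At the upper end of that range most patients could register improvement and the loss is much smaller.

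This is a loss of information on one secondary endpoint of a pilot. It is not a contradiction or a numerical error, and it does not touch the primary endpoint or the other neuropathy scales. It merits a change because the change costs almost nothing.

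**What to change.** In Section 14.0, keep the proportion at grade 3 or higher as a descriptive summary and add, for each arm at week 8 and at week 12:

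1. the proportion of patients improved by at least one CTC grade from baseline, with an exact 95% confidence interval;
2. the proportion worsened by at least one grade, with an exact 95% confidence interval;
3. the full distribution of grades, with the baseline distribution beside it.

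The baseline distribution will also show how many patients could have moved on the grade 3 or higher summary, so that summary can be read properly.

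**Cost.** A few lines of analysis text and slightly more tabulation. The grades are already scheduled at baseline, week 8 and week 12, so no visit, form or patient is added.

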this theory are lacking. The Conditioned Pain Modulation (CPM) protocol has been used to assess the intactness of the descending pain inhibition pathway. Decreased pain inhibition has been found in many patients with idiopathic pain syndrome. CPM has been shown to predict the efficacy of duloxetine in treating painful diabetic neuropathy as patients with ineffective CPM benefit more from duloxetine. We propose incorporating a CPM protocol into our trial to: 1) describe the CPM pattern in patients with CIPN; 2) explore whether baseline CPM patterns predict response to acupuncture in CIPN patients; and 3) explore if acupuncture treatment improves CPM. This will help us better understand a mechanism of acupuncture analgesia and advance the field of acupuncture and CIPN research.

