### **Treatment Expectancy Scale (TES)**

Pre-randomization treatment expectancy will be assessed using a validated measure. The Treatment Expectancy Scale (TES) is a 4-item instrument developed by [name] (co-PI) et al. TES is scored by adding up the score of each 4 items, with 1 indicating “Not at all agree” and 5 indicating “Completely agree” with the expected improvement as result of acupuncture. The score of instrument ranged from 4 to 20 out of a possible 4 to 20, with higher scores indicating greater expectancy. Outcome expectancy has long been considered an important predictor of treatment outcomes and has gained important consideration in acupuncture in recent years. It has demonstrated reliability (Cronbach’s  $\alpha$  of 0.82) and validity and is positively correlated with patient self-reported efficacy and satisfaction. The TES has also been validated in breast cancer survivors and is sensitive to change over time in response to acupuncture treatment. In our previous study, we found expectancy was stable overtime in the waitlist control group. Baseline expectancy predicted treatment outcomes of acupuncture. The TES will also be administered at weeks 4, 8, and 12. (Appendix A)

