neuropathy we will use linear regression to assess the association between NRS and TT, VT, and THT at baseline, and the association between change in NRS with change in TT, VT, and THT. For the mechanistic studies, we will use an interaction term between baseline CPM and real acupuncture to predict NRS at 8 weeks:  $NRS_8 = \beta_1 NRS_0 + \beta_2 CPM_0 + \beta_3 \text{Real Acupuncture} + \beta_4 CPM_0 \times \text{Real Acupuncture} + c$ . We will also test acupuncture-induced changes in CPM as  $CPM_8 = \beta_1 CPM_0 + \beta_2 \text{Real Acupuncture} + \beta_3 \text{Any Acupuncture} + c$ . We will also explore the relationship between treatment expectancy and response adjusting for baseline CIPN and treatment arm using multivariable linear regression comparing acupuncture versus sham acupuncture:  $NRS_8 = \beta_1 NRS_0 + \beta_2 \text{Real Acupuncture} + \beta_3 \text{Treatment Expectancy} + c$ . We will also estimate the change in mean HADS, BFI and ISI scores from baseline to 8 and 12 weeks along with a 95% confidence intervals, separately. We will also estimate the proportion of patients with a dose reduction and the proportion of patients who experience a dose escalation of neuropathy medication during the course of the 12 weeks along with an upper 90% confidence interval. All analyses will be by intent to treat, with participants analyzed according to allocation irrespective of treatment actually received. We will use multiple imputation, including 4 week outcome, for missing data at 8 weeks. Patients with 4 and 8 week outcomes are missing, they will not be included in the analysis.

For a trial with 25 patients per group, and an anticipated correlation between baseline and follow-up measures of 0.5, we will be able to calculate the upper bound of a one-sided, 90% confidence interval for the coefficients of any treatment and real acupuncture to approximately 0.35 standard deviations.

Last year, 935 solid tumor survivors had a diagnosis of persistent CIPN 3 months after chemotherapy completion. A recent study showed that among breast cancer survivors 28% reported moderate to severe CIPN 3 months after chemotherapy completion. Therefore, we anticipate 262 patients are eligible per year for our proposed study. Assuming at least a 15% enrollment rate of the eligible patients the estimated accrual is 3-4 patients per month, the estimated accrual period is between 19 and 25 months in order to identify 75 eligible patients.

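### The treatment-expectancy model for week 8 NRS omits the symptom-type terms that the primary model uses for the same outcome, so its slope can be confounded by symptom type (minor)

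*Protocol*

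**What the plan says.** Section 14.0 of the protocol sets a rule for the patient-reported outcomes, NRS among them: "analysis will be by ANCOVA with the baseline score and most bothersome CIPN symptom as covariates". The primary equation for week 8 NRS follows it and ends with two symptom dummies, pain being the reference: "\beta_4 \text{Tingling} + \beta_5 \text{Numbness} + c". Section 15.2 also makes symptom type a stratification factor.

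The same section then writes two further equations for week 8 NRS.

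- **Expectancy**, in the acupuncture and sham arms. The stated purpose is to "explore the relationship between treatment expectancy and response adjusting for baseline CIPN and treatment arm using multivariable linear regression". After baseline NRS the equation holds only "\beta_2 \text{Real Acupuncture} + \beta_3 \text{Treatment Expectancy} + c".
- **Baseline CPM.** The text reads "we will use an interaction term between baseline CPM and real acupuncture to predict NRS at 8 weeks". After baseline NRS and baseline CPM the equation holds only "\beta_3 \text{Real Acupuncture} + \beta_4 CPM_0 \times \text{Real Acupuncture} + c".

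Neither equation has a symptom-type term, and no reason is given. Section 8.0 places the expectancy measure before allocation: "Pre-randomization treatment expectancy will be assessed using a validated measure".

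**The concern.** By Section 4.1 the endpoint is the score of whichever symptom troubles the patient most, so week 8 NRS measures a different complaint in different patients. The sponsor thought this important enough to stratify on it and to adjust for it in the primary model.

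For the randomised arm comparison, leaving symptom type out mainly costs precision. Expectancy is different: it is a characteristic that patients bring with them, and randomisation does not balance symptom type across its levels. If, say, pain patients expect more from acupuncture and also end with different week 8 scores, the expectancy coefficient absorbs that difference. The relation between expectancy and response is a listed secondary objective (Section 2.0), so the slope is likely to be reported and read.

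Baseline CPM is not randomised either, and Section 3.0 asks whether it predicts response to acupuncture. In that model, however, the main effect and the interaction have to be considered separately.

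**Working it through.** **Inputs from the protocol:** 25 patients per arm; correlation of 0.5 between baseline and follow-up; the model terms set out above. The plan states no figure for this point, so there is none to reproduce.

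**Assumptions not in the protocol:** each symptom type makes up one third of patients; one type (for example pain) differs from the rest by dx SD on the predictor and by dy on week 8 NRS; the true expectancy and CPM effects are zero; the expectancy score is the baseline one; the expectancy model uses n = 50 and the CPM model n = 75. False-positive rates are at a two-sided 5% level, a yardstick chosen here because the plan names no test for these models.

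**Step 1. Formula for the expectancy model.** With p = 1/3, p(1−p) = 2/9 = 0.222, and

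bias = dx·dy·p(1−p) / (1 + dx²·p(1−p)).

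In NRS points per within-type SD of expectancy:

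- dx = 0.5, dy = 1 point: 0.1111 / 1.0556 = 0.105
- dx = 1, dy = 2 points: 0.4444 / 1.2222 = 0.364

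The sign depends on the directions of the two links; only the size matters here.

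**Step 2. Simulation in NRS points** (residual SD 2 points, the same two scenarios as end points). Two separate sets of runs gave a false slope of 0.11 to 0.38 with 7% to 25% false positives, and of 0.10 to 0.37 with 6% to 24%. With the symptom terms added, the slope was about 0 and the error rate 4% to 5%.

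**Step 3. Simulation in SD units of NRS** (3000 runs, baseline correlation 0.5).

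| dx = dy (SD) | Formula | Slope as written (false positives) | With Tingling and Numbness |
|---|---|---|---|
| 0.3 | 0.020 | 0.020 (5.1%) | 0.000 (4.9%) |
| 0.5 | 0.053 | 0.049 (6.3%) | −0.004 (4.5%) |
| 0.8 | 0.125 | 0.123 (15.4%) | −0.002 (5.2%) |
| 1.0 | 0.182 | 0.181 (27.0%) | −0.002 (4.6%) |

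If symptom type is linked to only one of expectancy and outcome (0.5 SD on one, 0 on the other), the slope is about 0 and the rate 4.8% to 5.2%.

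**Step 4. CPM model when symptom type shifts only the level of week 8 NRS** (SD units).

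| dx = dy | CPM main effect as written | Main effect with dummies | Interaction as written |
|---|---|---|---|
| 0.5 | 0.057 (6.9%) | 0.004 (5.3%) | −0.002 (5.7%) |
| 0.8 | 0.126 (16.1%) | 0.001 (5.2%) | −0.001 (4.2%) |
| 1.0 | 0.185 (30.3%) | 0.001 (4.7%) | −0.007 (4.6%) |

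The omission biases the main effect. It leaves the interaction, which is the planned term, unbiased.

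**Step 5. CPM model when symptom type changes the response to real acupuncture.** Here dx is the CPM gap and the second link is the difference in acupuncture effect; the interaction coefficient is shown.

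| Links | As written | With dummies only | With symptom type × Real Acupuncture too |
|---|---|---|---|
| 0.5 | 0.048 (6.4%) | 0.050 (6.4%) | −0.001 (5.4%) |
| 0.8 | 0.123 (9.3%) | 0.126 (8.6%) | 0.002 (4.7%) |
| 1.0 | 0.182 (15.0%) | 0.185 (14.2%) | −0.002 (4.9%) |

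In this case the primary model's dummies do not help; only the product with Real Acupuncture does.

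**The case against.** **The links are assumed.** Nothing in the protocol shows that tingling, numbness and pain patients differ in expectancy. At 0.3 SD the false-positive rate is 5.1%, in effect nominal. This stands: the protocol leaves the confounding possible but does not demonstrate it.

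**The aims are exploratory.** The protocol speaks of exploring and predicting, and a marker may legitimately predict partly because it tracks symptom type. This stands in part. The expectancy model already adjusts for baseline severity and arm, so it is not a plain correlation, and a reader will take the slope as the contribution of expectancy itself.

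**An SAP could add covariates.** It could, but the protocol writes the equation out and names its adjustment set. An SAP that followed it would keep the omission.

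**A stronger reading of the CPM model is tempting.** A reader might infer that dropping the primary model's symptom terms also distorts the CPM by real acupuncture interaction, and that restoring them would cure it. Steps 4 and 5 show neither is so. A reader might also take Section 3.0, "Decreased pain inhibition has been found in many patients with idiopathic pain syndrome", as evidence that CPM differs between pain-dominant and numbness-dominant patients. That sentence concerns other conditions and compares no CIPN subgroups. Even in the most extreme simulated case (a 1 SD gap in CPM and a 2-point gap in acupuncture effect), the false interaction of up to 0.40 NRS points per SD is below its standard error of about 0.5.

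**Conclusion.** The point holds for the expectancy model. Its equation departs, without explanation, from the covariate rule that the same section sets for NRS, and the omitted variable is a stratification factor while the predictor is not randomised. The size is conditional: about 0.1 NRS points per SD of expectancy with 6% to 7% false positives if the type differs by 0.5 SD in expectancy and 1 point in NRS, and about 0.4 with about 25% if it differs by 1 SD and 2 points. If either link is absent, there is no bias.

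For the CPM model the omission matters only for the CPM main effect. The interaction is exposed only if real acupuncture works differently by symptom type, which is a separate question from the mismatch with the primary model.

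Both models are exploratory. The primary ANCOVA and the planning estimates for the next trial do not use them, so the priority is minor.

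**What to change.** In Section 14.0:

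1. Add the Tingling and Numbness terms, coded as in the primary equation, to the expectancy equation, and name symptom type in the sentence that lists the adjustment.
2. Add the same two terms to the baseline CPM equation, for consistency and to protect the CPM main effect.
3. For the CPM model, report a sensitivity analysis that also includes symptom type (pain versus not pain) × Real Acupuncture.

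If the sponsor prefers the shorter equations, it should give the reason.

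The cost is wording. Symptom type is already recorded for stratification. The expectancy model goes from 4 to 6 coefficients (residual degrees of freedom 50 − 4 = 46 to 50 − 6 = 44). The CPM model goes from 5 to 7, or to 8 in the sensitivity analysis (75 − 5 = 70 to 68 or 67). In simulation the standard error went from about 0.27–0.33 to about 0.30 for expectancy, and from about 0.47–0.53 to about 0.53 for the CPM interaction with all terms added, so little precision is lost.

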### **Numeric Rating Scale (NRS)**

The primary endpoint will be measured by NRS of the most bothersome CIPN symptom. The numeric rating scale is an 11-point numeric scale with 0 representing no symptoms and 10 representing the worst symptoms imaginable. The NRS has been widely used to measure severity of symptoms, especially pain. Its high reliability and validity has been observed in prior studies. In clinical trials for multiple conditions, i.e. diabetic neuropathy, chronic low back pain, a reduction of 2 points or 30% on the NRS scores has been shown to be clinically significant. The NRS is a valid and reliable scale to measure CIPN symptoms (pain, tingling, numbness) intensity. It

is simple and can be administered both verbally and in writing, and is effective as an initial screening tool to assess patient's eligibility for the trial. The components of this measurement can be found in the Appendix A. It will be collected at baseline and at weeks 4, 8, and 12 for the acupuncture group and sham acupuncture group. The usual care control group will complete the questionnaire at baseline and weeks 4, 8 and 12. It takes no more than 2 minutes to complete. Week 4 questionnaires for the usual care group may be completed over the phone.

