If the confidence interval for acupuncture treatment effect includes clinically relevant effects, we will then perform a sample size calculation of a future two arm randomized trial using estimates of standard deviation of the CIPN score, the correlation between baseline and followup measures from the current trial. We will calculate the accrual rate along with a 95% Poisson confidence interval (with an exact 95% confidence interval). With a sample size of 75 patients the 95% confidence interval for the accrual rate will be  $\pm 23\%$ . Combining the resulting sample size with the accrual rate will provide an estimate of trial duration, along with an upper and lower bound.

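### The one-sided upper bound specified for the treatment coefficients leaves the benefit side of the NRS open, so the rule for planning the next trial cannot fail if it uses that interval

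*Protocol*

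**What the plan says.** Section 14.0 of the protocol sets the primary model: "analysis will be by ANCOVA with the baseline score and most bothersome CIPN symptom as covariates". For the primary endpoint it regresses week 8 NRS on baseline NRS, Real Acupuncture, Any Acupuncture and two symptom indicators. On treatment coding it says that "the three groups will be coded 1/1, 0/1, and 0/0 for acupuncture, Sham acupuncture, and UC respectively". Taken in the order of the model equation (Real, then Any), the Real coefficient is acupuncture minus sham and the Any coefficient is sham minus usual care.

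The precision statement begins "For a trial with 25 patients per group, and an anticipated correlation between baseline and follow-up measures of 0.5" and promises the "upper bound of a one-sided, 90% confidence interval for the coefficients of any treatment and real acupuncture to approximately 0.35 standard deviations". The decision rule follows in the same section: "If the confidence interval for acupuncture treatment effect includes clinically relevant effects, we will then perform a sample size calculation" for a future two-arm trial.

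Section 8.0 gives the direction of the NRS, with "0 representing no symptoms and 10 representing the worst symptoms imaginable". It also says that in other conditions "a reduction of 2 points or 30% on the NRS scores has been shown to be clinically significant". The same section says that higher FACT/GOG-Ntx neurotoxicity scores mean better function and fewer symptoms.

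**The concern.** The question behind the rule is whether a worthwhile benefit is still plausible after the pilot. That question needs the limit of the interval on the benefit side. The protocol fixes the side as upper, for coefficients on a scale where benefit is negative. A one-sided interval of that kind has no limit on the benefit side, so it can never exclude a worthwhile benefit.

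This rule is the pilot's only stated condition for going on to plan the definitive trial. If it cannot fail, it carries no information. The stated width of 0.35 SD also did not seem to follow from the inputs given with it.

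**Working it through.** **Inputs from the protocol.** 25 patients per arm, baseline to follow-up correlation r = 0.5, one-sided 90% level and ANCOVA (section 14.0); direction of the NRS (section 8.0). The protocol gives no SD for the NRS and no dropout rate.

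**Direction of the bound.** Higher NRS is worse, so benefit means a coefficient below zero. A one-sided interval with an upper bound only is (−∞, U], where U is the estimate plus the half-width. Suppose acupuncture came out 0.5 SD worse than sham. With a half-width of about 0.32 SD, U = 0.5 + 0.32 = 0.82 SD, and the interval still contains a benefit of 2 points, or of any size. The chance of meeting the rule is 100% under any true effect.

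The benefit side differs by outcome, although one ANCOVA form serves all three:

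| Outcome | Higher score means | Benefit-side limit |
|---|---|---|
| NRS (primary) | worse | lower |
| NPS | worse | lower |
| FACT/GOG-Ntx | better | upper |

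The single term in section 14.0, upper bound, fits only the last row.

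**The stated width.** Each coefficient contrasts 25 with 25 patients.

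- SE = √(2/25) × √(1 − 0.5²) = 0.2828 × 0.8660 = 0.2449 SD.
- Half-width, normal quantile: 1.2816 × 0.2449 = 0.314 SD.
- Half-width, t quantile with 75 − 6 = 69 df: 0.317 SD.
- Simulation of the full six-parameter model (20,000 runs): mean 0.323 SD.

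The stated 0.35 is not reproduced. Other readings of the inputs miss it too:

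| Variant | Half-width (SD) |
|---|---|
| Unadjusted, or change score at r = 0.5 | 0.362 |
| ANCOVA, two-sided 90% | 0.403 |
| ANCOVA, both needle arms (50) vs usual care (25) | 0.272 |
| ANCOVA, 20 per arm, r = 0.5 | 0.351 (t: 0.355) |

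Solving for 0.35 under ANCOVA gives n = 2 × 0.75 × (1.2816/0.35)² = 20.1 per arm at r = 0.5, or r of about 0.26 at 25 per arm.

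**What a benefit-side rule would do.** With the lower limit and a threshold of X points, the rule is met when the estimate minus 1.2816 × SE is at or below −X. So P(met) = Φ((−X + 1.2816 × SE − true effect)/SE), with SE = 0.2449 × SD. The SDs and thresholds below are assumptions. If acupuncture truly equals sham:

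| Assumed NRS SD | X = 1 point | X = 2 points |
|---|---|---|
| 1.5 | 7.5% | 0.0% |
| 2.0 | 22% | 0.3% |
| 2.5 | 36% | 2.4% |
| 3.0 | 47% | 7.5% |

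When the true benefit equals X, the rule is met 90% of the time in every row. Such a rule can fail, and how often depends strongly on X.

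**The case against.** The strongest reply is that the rule does not name its interval. It speaks of the acupuncture treatment effect, and section 14.0 describes the aim as reducing symptoms. If effect means the size of the reduction, the upper bound is the largest plausible benefit and the rule is a coherent test that can fail. That may well be what was intended. It stands as a reason to word the point conditionally. It does not clear the text, because the interval is stated for coefficients, and the model equation and the scale fix their sign.

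Some stronger inferences should not be drawn. A reader might conclude that the rule is always met in any event; this is so only if it uses the interval on the signed coefficient. A reader might say that the pilot would recommend a definitive trial even if acupuncture were no better than sham; the rule only triggers a sample size calculation. Nor is the contrast wholly open, since section 14.0 says that the planned trial compares acupuncture with sham, which points to the Real Acupuncture coefficient. The numerical threshold could reasonably be left to a statistical analysis plan, so its absence alone is no fault.

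On the width, the text says approximately and errs on the wide side. Patients missing both week 4 and week 8 are left out, so fewer than 25 per arm may be analysed. About 20 per arm would explain 0.35, but no such loss is stated.

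**Conclusion.** The text is wrong as written, and correcting it costs only wording. For NRS and NPS the specified bound is on the side of harm or least benefit, and it is the benefit side only for FACT/GOG-Ntx. Applied to the interval that section 14.0 specifies, the rule has a 100% chance of being met. That conclusion rests on one condition, that the rule uses the interval on the signed coefficient. No other interval is specified for these coefficients.

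The width is a minor correction: 0.31 to 0.32 SD from the stated inputs against 0.35 SD stated, a gap of about 0.03 to 0.04 SD in the conservative direction. A reader might infer that the trial's reported intervals will be misstated or that its precision is oversold. Neither follows: the reported intervals will come from the trial data, and the planning figure is pessimistic. The probabilities for a benefit-side rule depend on an assumed SD and threshold and hold only as a range.

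**What to change.** In section 14.0:

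1. State that the rule applies to the primary endpoint, NRS at week 8, and to the Real Acupuncture coefficient (acupuncture minus sham).
2. Use the one-sided 90% lower confidence limit. Perform the sample size calculation only if that limit is at or below −X points, where X > 0 is set by the sponsor before the data are seen. The 2 points or 30% in section 8.0 describes a reduction in scores, not a difference between arms, so it should not be carried over without comment.
3. For secondary outcomes, report the benefit-side limit (lower for NPS, upper for FACT/GOG-Ntx) without using the same X, as the scales differ.
4. Restate the precision as about 0.32 SD with 25 evaluable patients per arm and r = 0.5, or about 0.35 SD if about 20 per arm are evaluable.
5. If the chance of meeting the rule is quoted, show it over a range of NRS SDs.

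The cost is a few sentences. The design, the sample size and the ANCOVA stay as they are. The one real consequence is that the rule can then fail.
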